### Phase IV: Testing the Intervention

Phase IV will test the feasibility of the intervention. During phase IV, trained providers will deliver the intervention as revised in phases I to III as part of regularly scheduled consultations with clients in one of the study populations. To test the feasibility of the intervention during this phase, providers and clients will be followed for 6 months and participate in a variety of study activities. Providers will participate in knowledge, attitude, and practice (KAP) surveys, and a subset will participate in intervention observations. Intervention observations are intended to assess the fidelity to the intervention. Clients will participate in pre-post surveys and exit interviews upon completion of an intervention session. Separate measures are used to elicit data on the intervention from providers and clients (eg, willingness to participate in the intervention).

### Knowledge, Attitude, and Practice Surveys for Providers

Prior to beginning training, providers will complete KAP surveys that will serve as the pretest for the intervention. Follow-up KAP surveys will be administered to providers at 3 and 6 months posttraining in order to examine changes in the measures of interest. A 6-month follow-up period was chosen to facilitate measurement of short-term gains in MI techniques and identify changes in attitudes and perceptions about providing sexual health services to client populations. The surveys will cover 6 domains of the provider experience with the intervention, provider-client interaction, and the providers’ perceived utility of the intervention to both the provider and the client, including sociodemographic information, provider skills, efficacy and autonomy, competency and capacity, implementation, and attitudes. Provider intervention measures include indicators such as willingness to deliver the intervention and comfort with MI techniques (willingness), perceptions of the intervention’s impact on client behavior (satisfaction), perceptions of the intervention’s fit with the facility’s culture and clinical requirements (acceptability), and ability for the study site to continue delivering the intervention after the research study concludes (intervention logistics).

### Intervention Observations

During phase IV, in-country study staff will observe 10% of BSC sessions to independently assess provider knowledge, practice, and fidelity to the BSC protocol as written. The goal of the intervention observations is to assess the degree to which providers retain fidelity to the study protocol and provide nonjudgmental care consistent with the technical principles of MI. In-country study staff will use a standardized checklist to determine fidelity to the BSC guide. The checklist will include all the behavior skills taught in the training and the expected steps of the BSC session. During the observations, staff will be positioned so as not to interfere with the client-provider interaction, and the client will be asked if they consent to having the study staff member present. Intervention observations will collect quantitative data regarding provider ability to deliver the intervention protocol as written. Staff will check off skills as they are observed and record whether the steps of the BSC intervention are followed and are followed in order. At least two intervention observations per client type will be performed at each study site. Any issues regarding cultural sensitivity for key populations will be noted by study staff during the intervention observations. Providers who consistently demonstrate nonadherence to the intervention will be offered a 1-day refresher training for the intervention.

### Pre-Post Surveys With Clients

A convenience sample of clients from each study community will be recruited, and pre-post surveys will be administered prior to participation in the intervention (at baseline) and at 3 and 6 months postintervention. Adaptive, computer-assisted self-interviewing software with audioenabled playback will be used to address language barriers and issues of client literacy. The survey will take approximately 20 minutes to complete and include questions that assess (1) client sociodemographics and willingness, satisfaction, safety, and acceptability of the intervention (domains 1 to 5) and (2) client sexual health, including sexual competency and sexual behaviors (domain 6). Approximately 90% of questions will be the same across the key populations of clients; however, there will be some differences in questions regarding sexual behaviors depending on whether the outcome of interest is prevention of STIs, unintended pregnancy, or both.

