### Analysis of Quantitative Data From the Pre-Post Surveys and Exit Interviews

Data (client and KAP surveys and client exit interviews) will be deidentified and entered into the study database at each time point (0, 3, and 6 months). At each time point, descriptive statistics will be computed, and 3- and 6-month follow-up data will be compared with previous survey data. Appropriate tests of comparison (ie, *t* tests, chi-square tests, analyses of variance) will be used to determine differences in the primary (feasibility) and secondary (sexual health) outcome measures between time points. Although this phase is not powered to detect statistically significant differences in the sexual health outcomes, this analysis will provide information on whether the intervention is associated with differences in these outcomes from baseline to 3- and 6-month follow-up. Once collected by in-country study staff, the quantitative data from the intervention observations will be deidentified and entered into the study database.

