### Conclusions

Using brief interventions to reduce provider stigma and sexual risk behaviors among marginalized populations has the potential to be a cost-effective approach to improve sexual health in resource-constrained settings. The collection of formative, qualitative data that directly inform the content and delivery of the brief intervention may increase our understanding of how brief interventions can be delivered by health care providers in resource-limited health systems and different sociocultural contexts. Testing of the feasibility of the BSC in multiple settings and across multiple population groups will provide vital information on best practices for implementing brief interventions that are culturally sensitive and meet the needs of a range of vulnerable groups (eg, MSM or adolescent women). The data will also highlight factors shaping clinical practice among primary care providers and allow for the creation of more concrete, effective action plans designed to reduce sexual risk behaviors.

This feasibility study will determine whether the implementation of brief intervention programs aimed at improving sexual health outcomes is possible in the constraints of LMIC health systems. Understanding the ability of primary health care providers to deliver brief interventions and factors shaping clinical practice that will be investigated in this study is an important step in the improving the quality of sexual health services in resource-limited settings. While both provider and client perceptions of the feasibility of the intervention will be examined, adaptation of the intervention guide based on the feedback of the study populations and training providers on how to implement the final version of the BSC intervention will be performed during the study. However, careful attention will also be needed to the sustainability of the intervention. The current protocol will establish whether the integration of a BSC into routine patient visits is feasible. If proven feasible, strategies will need to be in place for sustainability, including routine trainings, training refreshers for providers, and close collaboration with key stakeholders (eg, ministries of health). Brief interventions will allow health care providers to improve the information available to clients, motivate and help them to develop risk-reduction skills that are seen as efficient ways to improve knowledge, change clients’ behavior, and reduce provider stigma regarding sexual health.

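### The primary feasibility outcomes are tested as change from a pre-exposure baseline, which satisfaction does not have and which for safety, acceptability and client willingness can only be anticipatory, so the tests cannot show feasibility

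*Protocol article*

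**What the plan says.** Four parts of the protocol article bear on this.

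- **Client timing and content (Pre-Post Surveys With Clients).** "pre-post surveys will be administered prior to participation in the intervention (at baseline) and at 3 and 6 months postintervention". The survey is described as one instrument that covers "willingness, satisfaction, safety, and acceptability of the intervention (domains 1 to 5"), plus a sexual health domain. The only variation in questions that is described is by client population and target outcome. No item is reserved for follow-up.
- **Provider timing and content (Knowledge, Attitude, and Practice Surveys for Providers).** "Prior to beginning training, providers will complete KAP surveys that will serve as the pretest for the intervention", with repeats at 3 and 6 months after training. The measures include "perceptions of the intervention’s impact on client behavior (satisfaction"), fit with the facility, willingness to deliver the intervention, and comfort with motivational interviewing (MI).
- **Analysis (Analysis of Quantitative Data From the Pre-Post Surveys and Exit Interviews).** Descriptive statistics are computed at each time point, and "3- and 6-month follow-up data will be compared with previous survey data". Then t tests, chi-square tests and analyses of variance "will be used to determine differences in the primary (feasibility) and secondary (sexual health) outcome measures between time points".
- **Conclusion to be drawn (Discussion, Conclusions).** "The current protocol will establish whether the integration of a BSC into routine patient visits is feasible".

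**The concern.** The article names feasibility as the primary outcome and change between time points as the way to test it. Two things do not fit.

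First, part of what is to be compared with time 0 does not exist at time 0. A client cannot be satisfied with a session that has not taken place. A provider who has not been trained has no basis for judging what the intervention did for clients.

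Second, feasibility is a question of level: is the intervention acceptable, safe and satisfactory enough to be used? A significant rise can end at a poor level, a significant fall can end at a good one, and a high and steady level gives no significant result at all. If the tests are taken as the primary evidence, they can point the wrong way for the yes-or-no statement that the study intends to make.

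**Working it through.** **Step 1. What time 0 can hold.** Survey timing is set against each feasibility measure.

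| Measure | Value at time 0 | 0 v 3 and 0 v 6 months |
|---|---|---|
| Client satisfaction | None; session not yet received | No valid baseline |
| Provider satisfaction (perceived impact on clients) | None; not yet trained | No valid baseline |
| Client-rated safety | Expected safety only | Expectation v experience |
| Acceptability (client view; provider view of facility fit) | Expected only | Expectation v experience |
| Client willingness | Expected only | Expectation v experience |
| Provider comfort with MI | Exists before training | Valid pre-post measure |

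Of the three pairwise contrasts (0 v 3, 0 v 6, 3 v 6), only 3 v 6 compares experience with experience. It shows whether a rating lasts, not whether it is adequate.

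**Step 2. Does a test of change follow feasibility?** The article gives no phase IV survey size, significance level, power or effect size, so there is no figure of its own to reproduce. Everything below is an assumption made for illustration: n = 50, 100 or 200 per time point, two-sided 0.05, and the two time points treated as independent samples of equal size.

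Power = Φ[(|p₁ − p₂| − 1.96·SE₀) / SE₁], where SE₀ = √[2p̄(1 − p̄)/n], SE₁ = √[(p₁(1 − p₁) + p₂(1 − p₂))/n] and p̄ = (p₁ + p₂)/2.

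Worked case, 20% to 40% at n = 100:
- p̄ = 0.30
- SE₀ = √(0.42/100) = 0.0648
- SE₁ = √(0.40/100) = 0.0632
- (0.200 − 1.96 × 0.0648)/0.0632 = 1.15, so power = 0.88

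| Assumed rates | n = 50 | n = 100 | n = 200 | Level reached |
|---|---|---|---|---|
| 90% → 90% | 0.025 | 0.025 | 0.025 | High |
| 20% → 40% | 0.59 | 0.88 | 0.99 | Low |
| 95% → 80% | 0.62 | 0.90 | 0.996 | May be adequate |

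The first row is the chance of a significant result in a given direction when nothing changes. The test is most likely to signal in the two cases where its direction misleads about the level, and it is silent in the case that looks most feasible.

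**Step 3. What a level-based analysis gives.** The 95% half-width for one proportion is 1.96·√[p(1 − p)/n]. At an assumed 80%:
- n = 50: 1.96 × √(0.16/50) = 11.1 percentage points
- n = 100: 7.8 percentage points
- n = 200: 5.5 percentage points

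This uses no baseline value and can be read directly against a criterion.

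**The case against.** The best case on the other side has five parts.

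1. **The article does not say outright that satisfaction is asked at baseline.** The survey software is adaptive, and a schedule of items by round may sit in the full protocol or the instruments. That is possible. But the article describes one survey given at all three times, limits no item to follow-up, and says that the primary measures are compared between time points. If satisfaction is in fact asked only afterwards, the stated comparison with baseline cannot be made for it, so the analysis paragraph still needs correcting.
2. **Levels will be reported.** Descriptive statistics are planned at each time point, so high and stable acceptability would be visible. This stands. The article does not, however, make those levels the basis of the primary analysis.
3. **Other sources address feasibility.** Exit interviews record reactions straight after the session, observers check fidelity, and the study log counts people approached, agreeing and refusing. This stands. A reader might infer that the study can say nothing about feasibility, and the documents do not support that. The exit interviews are described as qualitative (although the analysis heading groups them with quantitative data) and number about 24 per community.
4. **Some measures can be asked in advance.** Phase I focus groups rate perceived safety and willingness after a role play, and provider comfort with MI can plainly rise after training. It would therefore be too strong to say that safety has no baseline of any kind, or that no feasibility measure can be compared with baseline. For safety, the weaker statement holds: the change mixes expectation with experience.
5. **Two further inferences are not supported.** One is that nobody has met the intervention before baseline; people from phases I to III may join phase IV. The other is that client willingness starts at a ceiling and can only fall; the article gives no baseline level, and consent to research is not the same as willingness to use the intervention.

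**Conclusion.** The point holds for the planned tests of the primary outcome. For satisfaction, among clients and providers alike, two of the three contrasts (0 v 3 and 0 v 6 months) have no valid baseline. For safety, acceptability and client willingness, the same two contrasts compare an expectation with an experience. The remaining contrast measures persistence. None of these tests can show that a level is good enough, so they cannot support the feasibility conclusion that the article announces. The descriptive statistics, exit interviews, observations and recruitment and retention counts can contribute to it.

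This rests on the article's own timing, survey content and analysis wording, and on reading the survey as the same instrument at each round apart from population-specific questions. The power and precision figures only illustrate the direction of the problem; their rates and sample sizes are assumed. The analysis should be changed before phase IV: it concerns the primary outcome, and the Results section reports progress only in phases I and II.

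**What to change.** In the quantitative analysis section:

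- Limit pre-post tests to measures that exist before exposure: provider skills, attitudes and comfort with MI, and client sexual health.
- Make the primary analysis of satisfaction, experienced safety and acceptability the post-exposure level at 3 and 6 months, with 95% confidence intervals, read against feasibility criteria fixed before phase IV starts. If anticipated ratings are kept at baseline, label them as such and report them descriptively.
- Report client willingness to take part from the existing log of people approached, agreeing and refusing, with a count of ineligible people added so that the denominator is those eligible.

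A short self-rating by clients straight after the session would give an early quantitative level, but it is optional; the repair does not depend on it.

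The cost is a reworded analysis paragraph, agreement on the criteria, and one extra tally on the recruitment checklist.

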### Exit Interviews

Exit interviews will qualitatively assess client reactions to the intervention and the research study. Interviews will be completed upon receiving the intervention in order for clients to discuss their immediate feelings and attitudes toward the intervention. Approximately 24 interviews lasting 45 to 60 minutes will be conducted per study community, approximately 6 per key client population, by a member of the local research team. Interviewers will use an identical semistructured interview guide translated into the local language. Exit interviews will address client satisfaction with and willingness to use the intervention and client perception of intervention acceptability and safety.

### Study Documentation

Data will be collected regarding the recruitment and retention of clients and providers. These data will be collected by in-country study staff at each site using standardized checklists that track the number of clients and providers approached, number of those who agree to participate in the study, number who refuse, and the main reason for refusal. Participant contact information will be collected in order to provide reminders for the follow-up surveys. During the follow-up period, client and provider subject identification numbers will remain consistent in order to track retention through the 6-month follow-up period. In case of attrition, an attempt will be made to collect data on the reasons for discontinuing the study.

### Ethics and Consent to Participate

The core BSC protocol was first submitted to the WHO Research Project Review Panel; after its technical approval in 2016, WHO ERC was consulted for a special evaluation of the ethical components, with the following approval in 2017: prior to participation in any study activities, all participants (providers, clients, and key informants) will provide written informed consent at all stages (phases I to IV) of the study. The informed consent forms are explained in detail, and participants are asked to read them in full before agreeing to sign. If the individual chooses to participate, they sign the informed consent form and are offered a copy of the signed form. They can choose to decline taking a copy of the form if there is any concern that this would create additional risks.

## Results

Phase I is currently underway in Moldova, and phases I and II were completed in Peru in late 2019. Results are expected for the feasibility study in 2021.

### Analysis of Phases I and III

All focus group discussions and in-depth interviews will be audiorecorded, transcribed verbatim, and deidentified. For the focus group discussions, a notetaker will be present and will indicate the order of speakers and the first few words that each speaker says in order for the transcriber to be able to differentiate between speakers. For all activities in phases I and III with the exception of cognitive interviewing, a thematic analysis of these transcripts will be completed, using elements of grounded theory [41] and building on the IMB model. This will include the systematic and consistent application of deductive and inductive codes to the text. Inductive codes will include themes that are explicit domains present in the interview and focus group discussion guides, and deductive codes will include salient themes that arise more organically in the data. Additionally, all inductive themes and codes will be grouped according to the constructs in the IMB model, including information, motivation, and behavioral skills.

A preliminary codebook will be developed with provisional definitions for each code. A team of 2 to 5 data analysts will apply the provisional codebook to a single transcript, and the coded transcripts will be merged for comparison. Analysts will examine and discuss discrepancies in coding, and the code definitions will be revised based on an examination of coding disagreement. The process will be repeated with the revised codebook until consistent agreement among coders is attained. This process will occur with transcripts from all data collection activities using the same codebook for transcripts across all data collection activities. Once the final codebook is established, codes will be applied to all transcripts, with at least 2 analysts coding each transcript.

Based on systematic close readings of coded text, analysts will create thick descriptions for each theme. These descriptions will identify common concepts, patterns, and unique statements that appear in the transcripts. Specific themes arising in phases I to III regarding content and delivery of the intervention will be used by the research team to further refine the intervention for phase IV, determine the best way to present content, and better understand provider/client attitudes and willingness to participate. While small changes will be site-specific in order to promote cultural sensitivity, larger changes will be implemented universally across study sites.

### Analysis of Phase II

Analysis of phase II will be completed separately from the in-depth interviews and focus group discussions. For each interview, interviewer notes will be synthesized and grouped into themes based on the content of the participant feedback. These themes will be used for making recommendations to improve the intervention. Specifically, these recommendations will involve possible changes to the phrasing and language of the intervention, with the goal of improving comprehension and acceptability of the intervention among providers and clients. While small changes in the language, phrasing, and delivery of the intervention will be site-specific in order to promote cultural sensitivity, larger changes will be implemented universally across study sites to maintain protocol fidelity.

### Analysis of Quantitative Data From the Pre-Post Surveys and Exit Interviews

Data (client and KAP surveys and client exit interviews) will be deidentified and entered into the study database at each time point (0, 3, and 6 months). At each time point, descriptive statistics will be computed, and 3- and 6-month follow-up data will be compared with previous survey data. Appropriate tests of comparison (ie, *t* tests, chi-square tests, analyses of variance) will be used to determine differences in the primary (feasibility) and secondary (sexual health) outcome measures between time points. Although this phase is not powered to detect statistically significant differences in the sexual health outcomes, this analysis will provide information on whether the intervention is associated with differences in these outcomes from baseline to 3- and 6-month follow-up. Once collected by in-country study staff, the quantitative data from the intervention observations will be deidentified and entered into the study database.

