### Study Sites

The feasibility study will be implemented across multiple countries and multiple study communities within each country. For the purposes of this protocol, the term study site refers to an individual primary health care center. Study populations in each study country will be selected according to national sexual health priorities within the bounds of the proposed client population and sexual health outcomes. All research, training, and intervention documents will be translated from English to the appropriate local languages by local research teams and then backtranslated to English and compared for accuracy.

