### Sample Size

Sample sizes are approximate and will differ by study country, study community, and study site. As the goals of this study are to inform the feasibility, willingness, and acceptability of the BSC protocol among providers and clients, sampling is not intended to maximize external validity or provide data that are generalizable. However, it is important that the feasibility data are reflective of a diverse range of opinions and lived experiences. In sampling for the feasibility study, a diverse sample will be sought in terms of age and locally specific race/ethnicity in order to gather a range of opinions regarding both the formative qualitative (phases I to III) and quantitative (phase IV) portions.

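### The tests named for change between 0, 3 and 6 months are generic: the article does not say they are paired, and none allows for clustering of change by provider or site.

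*Protocol article*

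**What the plan says.** Under Analysis of Quantitative Data From the Pre-Post Surveys and Exit Interviews, the article says that at each wave "3- and 6-month follow-up data will be compared with previous survey data". It promises appropriate tests and then lists them after *ie*, which introduces a full list rather than examples. The t test comes first, followed by "chi-square tests, analyses of variance) will be used to determine differences in the primary (feasibility) and secondary (sexual health) outcome measures between time points". It does not state the paired or the independent-sample form, and it names no method for clustering. It adds that the phase is not powered for the sexual health outcomes but will still inform whether the intervention is associated with change in them.

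The design is described in other sections:

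- **Clients** (Pre-Post Surveys With Clients): "pre-post surveys will be administered prior to participation in the intervention (at baseline) and at 3 and 6 months postintervention".
- **Providers** (Knowledge, Attitude, and Practice Surveys for Providers): a survey before training, then "Follow-up KAP surveys will be administered to providers at 3 and 6 months posttraining in order to examine changes in the measures of interest".
- **Linkage** (Study Documentation): "client and provider subject identification numbers will remain consistent in order to track retention through the 6-month follow-up period".
- **Delivery** (Phase IV: Testing the Intervention): "trained providers will deliver the intervention as revised in phases I to III as part of regularly scheduled consultations with clients".
- **Setting** (Study Sites): "The feasibility study will be implemented across multiple countries and multiple study communities within each country".

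**The concern.** The data have two features that the listed tests do not visibly address.

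1. **The same people are measured three times.** A test that treats the waves as separate groups overstates the standard error of change and can miss real change.
2. **Clients share a provider, and providers share a site.** The intervention works through how the provider communicates, and its content may be adapted by site, so change itself may differ between providers and sites. A test that treats every person's change as independent then understates the standard error.

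The tests cover the primary feasibility outcomes as well as the sexual health outcomes, so the caveat about power does not remove the issue. At stake is whether the reported p-values for change, and any intervals, mean what they say.

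**Working it through.** **Nothing to reproduce.** The article gives no phase IV survey sample size ("Sample sizes are approximate and will differ by study country, study community, and study site"), significance level, standard deviation, within-person correlation, intraclass correlation (ICC) or number of clients per provider. All values below are assumptions, used with a two-sided 5% level and the normal approximation.

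**Step 1: pairing ignored.** With n people at both waves, variance σ² and within-person correlation ρ, the variance of the mean change is 2σ²(1−ρ)/n. An unpaired test uses 2σ²/n.

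- SE ratio (used/true) = 1/√(1−ρ)
- Actual size = 2[1 − Φ(1.96/√(1−ρ))]
- Power where the paired test has 80% = Φ(2.80 − 1.96/√(1−ρ)), with 2.80 = 1.96 + 0.84

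| ρ (assumed) | SE ratio | Actual size | Power |
|---|---|---|---|
| 0.3 | 1.20 | 1.9% | 68% |
| 0.5 | 1.41 | 0.6% | 51% |
| 0.7 | 1.83 | 0.04% | 22% |

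Yes/no items were simulated: 100 people, 50% positive at both waves, 20,000 runs per setting. The Pearson chi-square test rejected a true null in 2.3%, 0.7% and 0.06% of runs at correlations of 0.3, 0.5 and 0.7. McNemar's test rejected in 5.0%, 5.3% and 4.7%.

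**Step 2: pairing handled, clustering of change ignored.** Let m be clients per provider and let the ICC refer to change scores.

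- Design effect DE = 1 + (m−1)·ICC
- Actual size = 2[1 − Φ(1.96/√DE)]

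| m | ICC of change | DE | √DE | Actual size |
|---|---|---|---|---|
| 5 | 0.01 | 1.04 | 1.02 | 5.5% |
| 10 | 0.05 | 1.45 | 1.20 | 10.4% |
| 20 | 0.10 | 2.90 | 1.70 | 25.0% |

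**Step 3: both ignored.** SE ratio (used/true) = 1/√((1−ρ)·DE).

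| ρ | m | ICC of change | Calculation | SE ratio | Actual size |
|---|---|---|---|---|---|
| 0.7 | 5 | 0.01 | 1/√(0.3 × 1.04) | 1.79 | 0.04% |
| 0.3 | 10 | 0.05 | 1/√(0.7 × 1.45) | 0.99 | 5.2% |
| 0.3 | 20 | 0.10 | 1/√(0.7 × 2.90) | 0.70 | 16.9% |

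Depending on the inputs, the combined test can be far too conservative, about right or clearly too liberal.

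**Step 4: which kind of clustering matters.** Write a client's response at wave t as a wave mean, plus a provider effect, a participant effect and error. If the provider effect is the same at every wave, it cancels when baseline is subtracted from follow-up. Only a provider (or site) effect that changes between waves inflates the error of the change. A mixed model with random intercepts alone would therefore leave the problem in Step 2 uncorrected.

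**The case against.** The strongest reply is that the article names families of tests, not versions of them. A t test can be paired, an analysis of variance can be a repeated-measures one, and McNemar's test is itself a chi-square test. The text promises appropriate tests, and constant identification numbers make linkage possible. This is also a condensed account of a master protocol, with country-specific protocols to follow, and the exact form of each test may stand in a document not shown.

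Much of that stands. A reader might infer that the plan has chosen independent-sample tests. The article does not say so, although the stated purpose of the constant numbers is to track retention, not to link responses for analysis. Nor can one conclude that the reported error bars will be wrong: no intervals are described, and every size above rests on assumed inputs. Because stable provider and site differences cancel, clustering matters only as far as change itself varies between clusters. The study is a nonrandomized feasibility study, not powered for its sexual health outcomes, and it also judges feasibility from interviews, observations and recruitment records.

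Two things are not answered. The list is given as complete, and even with every test read in its paired form, none of them in standard form handles clients nested in providers and sites. And a chi-square test without qualification is ordinarily Pearson's, which is not valid for the same people at two times.

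**Conclusion.** The point holds in a limited form. The named methods do not fully fit the design that the article describes: paired forms are left open, and allowance for clustering of change is absent on any reading.

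If pairing were ignored, standard errors would be 1.20 to 1.83 times too large (assumed ρ 0.3 to 0.7). If clustering of change were ignored, a nominal 5% test would have a size of about 5.5% to 25% (assumed 5 to 20 clients per provider, change-score ICC 0.01 to 0.10). The net effect cannot be determined from the document. This is a moderate point and a cheap improvement, not a fault that must be repaired before the study can proceed.

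**What to change.** Replace the list of tests with a statement to this effect:

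- Responses are linked across waves by participant ID.
- Change from baseline to 3 and 6 months is estimated with GEE or mixed models for repeated measures. The minimum is paired t and McNemar-type comparisons.
- Standard errors are clustered at provider or site level for client data and at site level for the provider surveys, with a correction for a small number of clusters.
- A mixed model, if used, includes provider-by-time or site-by-time random effects, not random intercepts only.
- Change is reported with 95% confidence intervals.

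Also make sure that the delivering provider's ID can be linked to each client record. The article does not describe the fields of the client form, so this may already be in place. If it is not, it may be hard to recover after phase IV.

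The cost is revised wording, slightly more analysis work and at most one extra field, with no added participants or visits. Intervals may be wider where clusters are few.
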